## **6.6 Concomitant medication and concomitant therapy**

For drugs administered concomitantly from Visit 1 to Visit 9 for treatment and diagnosis of other diseases or AEs, details of concomitant medication (product name, purpose of administration, dose and unit, duration of treatment [start date, stop date], route of administration, etc.) should be recorded in the case report form (CRF). During the period from after Visit 9 to Visit 11, only drugs administered for SAEs or AESIs will be documented.

Information on concomitant treatment (concomitant medication or therapy) given for treatment and diagnosis of other diseases or AEs during the study period should be recorded in the CRF.

For concomitant medication, product name, purpose of administration, dose and unit, duration of treatment (start date, stop date), and route of administration will be documented. For concomitant therapy, name of therapy, purpose, and duration (start date, stop date) will be documented.

Drugs listed below are prohibited for concomitant use during the period from Visit 1 to Visit 9.

- (1) Vaccines within 28 days before and after IP dosing
- (2) Immunosuppressants or immune modifying drugs
  - Azathioprine, cyclosporine, interferon, G-CSF, tacrolimus, everolimus, sirolimus, cyclophosphamide, 6-mercaptopurine, methotrexate, rapamycin, leflunomide, etc.
  - Long term use of steroids: prednisone  $\geq 10$  mg/day for  $\geq 14$  consecutive days (Topical or inhaled steroids, intranasal spray, and eye drops are allowed regardless of dose.)
- (3) Blood or blood derivatives (including immunoglobulin)
- (4) Anticoagulant therapy: continuous use of anticoagulants such as coumarin/warfarin or new oral anticoagulants/antiplatelets
  - New oral anticoagulants (direct oral anticoagulant [DOAC]): dabigatran, rivaroxaban, apixaban, edoxaban
  - New antiplatelets: prasugrel, ticagrelor, cangrelor

Drugs listed below are prohibited for concomitant use throughout the study period (Visit 1 to Visit 11).

- (1) Other coronavirus vaccines
- (2) Other IPs

Other concomitant drugs for treatment or examination of other diseases that are considered to have no impact on the interpretation of study results will be allowed at the discretion of the investigator.

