- 11) If possible, subjects who are withdrawn from the study will visit the institution for required procedures. Those who are withdrawn prior to Visit 9 (end of main study visit) will perform Visit 9 procedures. Those who are withdrawn after Visit 9 will perform Visit 11 procedures (end of follow-up visit) except for blood sampling for immunogenicity testing. If consent is obtained from the subject, telephone visits will be conducted by a trained sub-investigator who will call the subject at the time points of Visit 10 (Week 26 after the 2nd dose of the IP) and Visit 11 (Week 52 after the 2nd dose of the IP) for serious ADRs and AESIs. Subject who has not performed administration of 2nd dose investigational product will conduct Visit 10 and Visit 11 on the basis of scheduled date of 2nd dose administration.
- 12) Concomitant drugs administered for SAEs and AESIs will be collected.
- 13) Status of SAEs and AESIs will be checked. In the event of an AESI, additional tests may be conducted as necessary at the discretion of the investigator, and if necessary, the DSMB may meet to review the case for status of ADR and enhanced disease.

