#### **4.1.2 Immunogenicity assessment**

Subject has to keep fasting (prohibition of food or beverage except water for 8 hours) before blood

sample collection for immunogenicity assessment. At least 28mL at pre-dose (Visit 2), at least 25mL on Day 21 after the 1st dose (Visit 5), at least 25mL on Day 21 after the 2nd dose (Visit 8), and at least 5mL on Week 26 (Visit 10), and Week 52 (Visit 11) after the 2nd dose of blood samples will be collected. Each of 20mL of blood samples collected at Visit 2, Visit 5 and Visit 8 will be stored in appropriate container and at appropriate temperature to be sent to the central laboratory (Vaccine/Bio Research Institute at the Catholic University of Korea, College of Medicine).

Besides, blood samples collected at other visits will be stored at room temperature for at least 30 minutes to 2 hours for blood coagulation reaction. After the coagulation, blood will be separated to achieve serum by a centrifuge. Separated serum will be split into several and appropriate containers and stored at appropriate temperature before sending to the central laboratory (International Vaccine Institute).

Humoral immunity will be tested by the International Vaccine Institute, and cellular immunity will be tested by the Vaccine/Bio Research Institute at the Catholic University of Korea, College of Medicine. Samples for immunogenicity testing will be sent to the central laboratory designated for each test for collective measurement and analysis.

- **Humoral immunity testing (total volume of blood to be collected: at least 8 mL pre-dose (Visit 2), at least 5 mL at other visits)**

- 1) Antigen protein-specific antibody test using ELISA: approximately 3 mL of blood
  - To assess the titer of the antibody specifically binding to the RBD of the spike protein induced by the IP in the serum of the subject treated with the IP.

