**4.2.10 Visit 10 (interim visit for follow-up, 26 ± 2 weeks after the 2nd dose)**

This visit will take place at Week 26 after the 2nd dose of the IP. Procedures to be carried out during this visit are as follows.

- Any SAEs and AESIs since last visit will be checked. If the subject experienced SAEs and AESIs, concomitant medications given for these events will also be documented.
- Vital signs will be measured.
- A blood sample will be collected for immunogenicity testing.
- The next visit day will be scheduled.

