- 16) History of therapy that might affect immunity: treatment with immunosuppressants or immune modifying drugs, anticancer therapy, or radiotherapy within 3 months prior to screening
- 17) History of systemic steroids (prednisone  $\geq 10\text{mg/day}$  for  $> 14$  consecutive days) within 3 months prior to screening. Topical, inhaled, and intranasal corticosteroids are allowed regardless of dose.
- 18) Past treatment within 3 months prior to screening, or planned treatment during the study period, with immunoglobulin or blood derivatives
- 19) Individual with thrombocytopenia or other coagulation disorders for whom intramuscular (IM) injections are contraindicated or individual who is on anticoagulant therapy\*  
\* Anticoagulant therapy: continuous use of anticoagulants such as coumarin/warfarin or new oral anticoagulants/antiplatelets
- 20) History of excessive alcohol consumption or drug addiction
- 21) Women of childbearing potential who do not agree to use medically allowed methods of contraception\* or to be heterosexually inactive until 60 days after the last dose of the IP  
\*Hormonal contraceptive, intrauterine device(IUD(intrauterine device) or IUS(intrauterine system)), tubal ligation, double-blocking method(condom for male and female, cervical cap or diaphragm, complex method such as contraceptive sponge), single-blocking method using spermicides
- 22) Pregnant or breastfeeding woman

- 23) Treatment with other IPs within 6 months prior to participation in this study
- 24) The investigator who is directly related to this study or sub-investigator/study coordinator who is supervised by investigator or their family member
- 25) Other reasons including medical reasons based on which the individual is considered to be ineligible for this study in the opinion of the investigator

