#### Major protocol deviations

- ① Informed consent form (ICF) not obtained
- ② Violation of the inclusion/exclusion criteria
- ③ Concomitant treatment with prohibited drugs during the study period
- ④ Baseline and Visit 8 immunogenicity tests not done
- ⑤ Randomization errors

For subjects who are considered to have any major protocol deviations other than the above listed,

a blind meeting will be held prior to database (DB) lock in which a decision will be made on whether to exclude the subjects from the PPS based on comprehensive assessment of the impact of the deviations on the study.

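### Other coronavirus vaccines are prohibited to Visit 11, but after Visit 9 the protocol does not systematically record them, so the Week 26 and Week 52 titres cannot be reliably screened for them

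*Protocol*

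**What the plan says.** Section 6.6 has two prohibition lists. The first runs from Visit 1 to Visit 9. The second contains other coronavirus vaccines and other investigational products, and is introduced with "Drugs listed below are prohibited for concomitant use throughout the study period (Visit 1 to Visit 11".

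The recording rule in the same section is narrower: "During the period from after Visit 9 to Visit 11, only drugs administered for SAEs or AESIs will be documented". It is repeated in three places:
- Schedule of Assessments, note 12 (attached to the concomitant-medication entry at Visits 10 and 11): "Concomitant drugs administered for SAEs and AESIs will be collected".
- Section 4.2.10 (Visit 10): "If the subject experienced SAEs and AESIs, concomitant medications given for these events will also be documented".
- Section 4.2.11 (Visit 11): the same instruction.

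Two other sentences point to wider recording. The second paragraph of 6.6 says that concomitant treatment "given for treatment and diagnosis of other diseases or AEs during the study period should be recorded in the CRF". Section 4.1.3.3 says in general terms that changes in medication since screening are checked and that their details go into the source document; it names no last visit.

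Immunogenicity blood continues to be drawn after Visit 9: "at least 5mL on Week 26 (Visit 10), and Week 52 (Visit 11". Section 7.2.2 lists GMT, GMFR and seroconversion rate at both times as endpoints for both parts. Section 7.3.1 lists as a major deviation, for which a subject may be excluded from the PPS: "Concomitant treatment with prohibited drugs during the study period".

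**The concern.** A prohibition that feeds an analysis-set rule needs data showing who broke it. Here the prohibition and the titre endpoints run to Visit 11, while routine recording of the relevant exposure stops at Visit 9.

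As the protocol describes them, the ELISA measures antibody binding to the RBD and the FRNT measures neutralisation of wild-type virus. Neither is described as telling antibody induced by EuCorVac-19 from antibody induced by another coronavirus vaccine. An unrecorded vaccination between Visit 9 and the Week 26 or Week 52 sample could therefore appear as persistence in a EuCorVac-19 group, or as seroconversion in the placebo group. The results exposed are the late GMT, GMFR and seroconversion rates, including the Part A interim analysis at Week 26 and the final analysis of both parts at Week 52.

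A statistical analysis plan that is not shown may well contain a rule for such titres. It could not apply the rule to exposures that the protocol does not collect.

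**Working it through.** **Is a preventive vaccine captured after Visit 9?**

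| Place | What is recorded after Visit 9 | Does it reach a preventive vaccine? |
|---|---|---|
| 6.6, first paragraph | Drugs given for SAEs or AESIs only | No |
| Schedule, note 12 | Same | No |
| 4.2.10 and 4.2.11 | SAEs, AESIs and drugs given for them | No |
| 6.6, second paragraph | Treatment or diagnosis of other diseases or AEs, during the study period | Not clearly; prevention is neither |
| 4.1.3.3 | Any change in concomitant medication, in the source document | Possibly, but not in the CRF, and not repeated at Visits 10 and 11 |

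The visit lists support the narrow reading. Sections 4.2.3 to 4.2.9 each ask about any change in concomitant medication since the last visit. Sections 4.2.10 and 4.2.11 drop that item.

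**Length of the gap** (visit days and windows from the Schedule)
- Nominal: Week 52 is day 364 and Visit 9 is day 28 after dose 2. 364 − 28 = 336 days = 48 weeks; 48/52 = 92% of follow-up after dose 2. Counted from dose 1: 336/(21 + 364) = 336/385 = 87%.
- With windows (Visit 9 +7 days, Visit 11 ±28 days): shortest 364 − 28 − 35 = 301 days; longest 364 + 28 − 28 = 364 days.
- Before the Week 26 sample: 182 − 28 = 154 days; with windows (Visit 10 ±14 days) 182 − 14 − 35 = 133 to 182 + 14 − 28 = 168 days.

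**Possible effect on the late results** (illustration; f and R are assumptions, not in the documents)

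Let a fraction f of a group have an unrecorded vaccination that multiplies titre by R on geometric average. The mean log titre rises by f·log R, so the group's GMT and GMFR are multiplied by R^f.

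| f | R = 5 | R = 10 |
|---|---|---|
| 10% | 5^0.1 = 1.17 | 10^0.1 = 1.26 |
| 30% | 5^0.3 = 1.62 | 10^0.3 = 2.00 |
| 50% | 5^0.5 = 2.24 | 10^0.5 = 3.16 |

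If every such subject seroconverts, a true rate s becomes s + f(1 − s). With s = 50% and f = 10% this is 0.50 + 0.10 × 0.50 = 55%. In the placebo group, with s near 0, it is about f.

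Among the 25 evaluable Part B placebo subjects planned in 7.1.1.2, the chance that at least one is affected is 1 − (1 − f)^25: 72% at f = 5% and 93% at f = 10%.

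**The case against.** The protocol is not silent on detection. Section 4.1.3.3 sends any change in concomitant medication to the source document without an end date. Sections 5.6 and 9.1 require deviations to be reported and documented, and subjects attend in person at Visits 10 and 11. A vaccination that a subject mentions can be documented and the subject excluded from the PPS. This stands, and it limits the point to detection. A reader might infer that nobody could ever apply the PPS rule, but the documents do not support that. They show that its use would depend on chance disclosure. The exclusion is also optional and confined to the PPS; the FAS, which is analysed additionally, has none.

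Three further readings are tempting and are not supported.
- That the same gap covers immunoglobulin and immunosuppressants. Their prohibition ends at Visit 9 as a stated design choice. As treatment for disease they fall within the second paragraph of 6.6. The exclusion criterion on "planned treatment during the study period, with immunoglobulin or blood derivatives" concerns what is planned at entry and does not contradict this.
- That an SAE or AESI following another vaccine could not be recognised. All SAEs are reported and followed up (8.4), and causality assessment must consider explanations other than the study product (8.3.2).
- That uptake would differ between groups. Part B is observer-blind and 6.5 withdraws subjects whose code is broken, so the documents give no basis for assuming a difference.

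The stakes are also limited. The study is exploratory and tests no hypothesis (7.1.2). Visit 8 is the only post-dose immunogenicity visit whose absence is a listed major deviation, and no late time point is named as primary. Section 1.1 says that no COVID-19 vaccine was yet approved in South Korea, although it also cites an emergency authorisation abroad and several Phase 3 programmes. How many subjects would have access to one is unknown from the documents.

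**Conclusion.** The point holds as an internal inconsistency in data collection. Other coronavirus vaccines and other investigational products are prohibited to Visit 11, but for nominally 48 of the 52 weeks after dose 2 no CRF or visit procedure systematically captures them. Section 4.1.3.3 only partly offsets this. The prohibited-drug deviation therefore cannot be applied reliably to the Week 26 and Week 52 GMT, GMFR and seroconversion rates.

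Titres up to Visit 8 and safety data up to Visit 9 are unaffected, because all concomitant drugs are recorded to that visit. The size of any bias is unknown: the R^f figures assume both the uptake and an average titre rise that does not depend on the existing titre. They show that moderate uptake could matter, not that it would occur. This is a should-fix point. It takes no position on which products should be prohibited or for how long.

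**What to change.** Reconcile 4.1.3.3, the two recording paragraphs of 6.6, Schedule note 12, 4.2.10 and 4.2.11. They should state alike that any other coronavirus vaccine or other investigational product is asked about at Visits 10 and 11 and recorded in the CRF (product and date) up to Visit 11, whatever the reason for use.

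For the Week 26 and Week 52 analyses, apply the existing prohibited-drug deviation to titres drawn after such a product, and show the result with all titres alongside.

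The cost is a slightly longer concomitant-medication entry at two visits that already have one, and somewhat fewer late titres in the per-protocol analysis.

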## 7. Statistical considerations

### 7.1 Sample size and rationale for sample size calculation

#### 7.1.1 Sample size

##### 7.1.1.1 Part A

To obtain 25 subjects per dose group who have at least one dose of the IP after randomization, at least 50 eligible volunteers based on the inclusion/exclusion criteria will be enrolled.

|                                                | Low dose group | High dose group |
|------------------------------------------------|----------------|-----------------|
| Number of subjects in test group               | 15 subjects    | 15 subjects     |
| Number of subjects in placebo comparator group | 10 subjects    | 10 subjects     |
| Total number of subjects                       | 25 subjects    | 25 subjects     |

##### 7.1.1.2 Part B

To obtain 195 subjects who have at least one dose of the IP after randomization and are available for immune response analysis, at least 230 eligible volunteers based on the inclusion/exclusion criteria will be enrolled considering the drop-out rate of 15%. At least 15% (35 subjects) of overall subjects will be recruited from those between 51 and 75 years of age.

|                                                           | Low dose group | High dose group | Placebo comparator group |
|-----------------------------------------------------------|----------------|-----------------|--------------------------|
| Number of immune response analyses                        | 85 subjects    | 85 subjects     | 25 subjects              |
| Total number of subjects considering drop-out rate of 15% | 100 subjects   | 100 subjects    | 30 subjects              |

### 7.1.2 Rationale for sample size calculation

Because this is the first time that the IP is administered to humans and this exploratory study is not intended to test a statistical hypothesis, sample size was not statistically calculated.

### 7.1.3 Replacement of Study Subject

If the first 5 subjects in each dose group in Part A for safety assessment are decided to discontinue or withdraw the study without administration of IP after randomization, additional subject can be enrolled for replacement of discontinued or withdrawn subjects. These additional subjects will be allocated in identical group in which the subject who decided to discontinue the study was randomized using IWRS.

## 7.2 Endpoints

### 7.2.1 Safety endpoints

- AEs
  - ① Immediate AEs occurring within 30 minutes after each IP dosing
  - ② Solicited local and systemic AEs occurring for 7 days (Day 0~ Day 6) after each IP dosing
    - ✓ Local AEs : pain, tenderness, erythema/redness, induration/swelling, itchiness
    - ✓ Systemic AEs : fever, fatigue/malaise, chills/rigors, headache, myalgia, joint pain, diarrhea, vomiting, abdominal pain, mucocutaneous reaction/rash, cough, acute bronchospasm, respiratory distress
  - ③ Unsolicited AEs occurring within 28 days after the last IP dosing
  - ④ SAEs occurring within 52 weeks after the last IP dosing
  - ⑤ AESIs occurring within 52 weeks after the last IP dosing
- Clinical laboratory tests (hematology/blood chemistry, urinalysis)
- Vital signs
- Physical examination

### 7.2.2 Immunogenicity endpoints

#### 7.2.2.1 Part A

- GMT and GMFR of antigen protein-specific antibodies as measured by ELISA at pre-dose (Visit 2), on Day 21 (Visit 5) after the 1st dose, and on Day 21 (Visit 8), Week 26 (Visit 10), and Week 52 (Visit 11) after the 2nd dose of the IP
- Proportion of subjects with seroconversion to antigen protein-specific antibodies as measured

by ELISA on Day 21 (Visit 5) after the 1st dose and on Day 21 (Visit 8), Week 26 (Visit 10), and Week 52 (Visit 11) after the 2nd dose of the IP (Seroconversion rate [SCR]) †

† Seroconversion is defined as a  $\geq 4$ -fold increase in GMT post-dose of the IP from pre-dose.

- GMT and GMFR compared to the baseline of neutralizing antibodies to SARS-CoV-2 as analyzed by Focus Reduction Neutralization Test (Wild-type SARS-CoV-2) at pre-dose (Visit 2), on Day 21 (Visit 5) after the 1st dose, and on Day 21 (Visit 8), Week 26 (Visit 10), and Week 52 (Visit 11) after the 2nd dose of the IP
  - Proportion of subjects with seroconversion to SARS-CoV-2 neutralizing antibodies as analyzed by Focus Focus Reduction Neutralization Test (Wild-type SARS-CoV-2) at pre-dose (Visit 2), on Day 21 (Visit 5) after the 1st dose, and on Day 21 (Visit 8), Week 26 (Visit 10), and Week 52 (Visit 11) after the 2nd dose of the IP (Seroconversion rate [SCR])‡
- ‡ Seroconversion is defined as a  $\geq 4$ -fold increase in GMT post-dose of the IP from pre-dose

#### 7.2.2.2 Part B

- GMT and GMFR of antigen protein-specific antibodies as measured by ELISA at pre-dose (Visit 2), on Day 21 (Visit 5) after the 1st dose, and on Day 21 (Visit 8), Week 26 (Visit 10), and Week 52 (Visit 11) after the 2nd dose of the IP
  - Proportion of subjects with seroconversion to antigen protein-specific antibodies as measured by ELISA on Day 21 (Visit 5) after the 1st dose and on Day 21 (Visit 8), Week 26 (Visit 10), and Week 52 (Visit 11) after the 2nd dose of the IP (seroconversion rate [SCR])†
- † Seroconversion is defined as a  $\geq 4$ -fold increase in GMT post-dose of the IP from pre-dose.
- GMT and GMFR compared to the baseline of neutralizing antibodies to SARS-CoV-2 as analyzed by Focus Reduction Neutralization Test (Wild-type SARS-CoV-2) at pre-dose (Visit 2), on Day 21 (Visit 5) after the 1st dose, and on Day 21 (Visit 8), Week 26 (Visit 10), and Week 52 (Visit 11) after the 2nd dose of the IP
  - Proportion of subjects with seroconversion to SARS-CoV-2 neutralizing antibodies as analyzed by Focus Focus Reduction Neutralization Test (Wild-type SARS-CoV-2) at pre-dose (Visit 2), on Day 21 (Visit 5) after the 1st dose, and on Day 21 (Visit 8), Week 26 (Visit 10), and Week 52 (Visit 11) after the 2nd dose of the IP (Seroconversion rate [SCR])‡
- ‡ Seroconversion is defined as a  $\geq 4$ -fold increase in GMT post-dose of the IP from pre-dose

#### 7.2.2.3 Exploratory assessment (Part A & Part B)

- T cell immune response markers as analyzed by Ex vivo IFN $\gamma$  ELISpot at pre-dose (Visit 2), on Day 21 (Visit 5) after the 1st dose, and on Day 21 (Visit 8) after the 2nd dose of the IP

### 7.3 Statistical analysis plan

#### 7.3.1 Analysis sets

Safety data obtained from the study subjects will primarily be analyzed in the safety set while immunogenicity data will be analyzed primarily in the per-protocol set (PPS) and additionally in the full analysis set (FAS).

Analysis sets are defined as follows.

(1) Safety Set:

Includes all subjects who had at least one dose of the IP.

(2) FAS (Full Analysis Set):

Includes all subjects who had at least one dose of the IP, pre-dose immunogenicity data and at least one post-dose immunogenicity endpoint data available. Hence, the number of subjects may vary depending on the number of immunogenicity endpoints.

(3) PPS (Per-Protocol Set):

Includes all subjects in the FAS who completed the study through to Visit 9 (end of main study visit) according to the protocol. In the follow-up analysis, those who completed the study through to the end of follow-up visit (Visit 11) will separately be analyzed. Subjects with any of the following protocol deviations may be excluded from the PPS.

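### The per-protocol set depends on visits after the titre was drawn, and titres after infection or an outside coronavirus vaccine have no visit-specific rule and no required date

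*Protocol*

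**What the plan says.** Protocol section 7.3.1 analyses immunogenicity primarily in the PPS and additionally in the full analysis set (FAS). The PPS "Includes all subjects in the FAS who completed the study through to Visit 9 (end of main study visit) according to the protocol". For the follow-up analysis, "those who completed the study through to the end of follow-up visit (Visit 11) will separately be analyzed".

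A list of five major deviations follows, introduced by "Subjects with any of the following protocol deviations may be excluded from the PPS". Two of them matter here: "Concomitant treatment with prohibited drugs during the study period" and "Baseline and Visit 8 immunogenicity tests not done". SARS-CoV-2 infection is not on the list. A blind meeting before database lock considers major deviations that are not listed.

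Section 6.6 prohibits other coronavirus vaccines and other investigational products from Visit 1 to Visit 11. After Visit 9, the same section has only drugs given for SAEs or AESIs documented. At Visits 10 and 11 the event check is limited in the same way: "Any SAEs and AESIs since last visit will be checked". Scheduled COVID-19 tests take place at Visits 1 and 2 only (section 4.1.3.6).

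**The concern.** A per-protocol set for a titre should depend on what happened up to the blood draw. Here membership is fixed once per subject, by attendance at a later visit. Visit 9 takes no immunogenicity sample, yet missing it removes a subject whose two doses and Visit 2 and Visit 8 sera are all in order. Immune response is the primary objective of Part B, so the affected analysis is the main one.

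The opposite problem arises at the late visits. The assays measure IgG against the receptor-binding domain and neutralisation of wild-type virus. Neither distinguishes a response to the study vaccine from a response to infection, nor from a response to another spike-based vaccine. If such titres remain without a dated record of the exposure, the Week 26 and Week 52 results describe vaccine persistence and exposure together, and a later analysis plan could not reliably separate them.

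**Working it through.** **Plan's own figure.** The only arithmetic tied to the evaluable immunogenicity set is the 15% drop-out allowance in section 7.1.1.2: 85/0.85 = 100, 25/0.85 = 29.4, rounded up to 30, and 195/0.85 = 229.4, rounded up to 230. The stated enrolment reproduces. The protocol gives no infection rate, fold rise or late-withdrawal rate, so the inputs below are assumptions.

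**Timing of membership and samples.**
- Visit 8 falls on days 21–26 after dose 2 and Visit 9 on days 28–35. The Visit 9 condition therefore acts 2 to 14 days after the last main-study draw (28 − 26 = 2; 35 − 21 = 14).
- The deviation list already deals with a missing baseline or Visit 8 test, so the Visit 9 condition adds nothing about the titre itself.
- A Week 26 titre is drawn at Visit 10. If the follow-up set is Visit 11 completers, it is lost when the subject leaves between Visits 10 and 11. The protocol creates such exits through pregnancy (section 8.6) and code-breaking (section 6.5).
- Part A has its own Week 26 lock at Visit 10 (section 7.3.7), when Visit 11 completion is unknown. The same endpoint may thus rest on different sets at the interim and final analyses.

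**Effect of dropping valid titres.** If a share g is dropped whose GMT is k times that of the rest, PPS GMT / all-subject GMT = k^(−g).
- g = 0.01: k = 0.5 gives 1.007; k = 2 gives 0.993.
- g = 0.02: k = 0.5 gives 1.014; k = 2 gives 0.986.
- g = 0.15, an extreme equal to the whole drop-out allowance: 1.11 and 0.90.

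If k = 1 there is no bias, only a loss of subjects.

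**Effect of keeping titres after infection.** If n_i of n subjects have titres raised r-fold, the group GMT is multiplied by r^(n_i/n). Section 4.1.2 sets FRNT50 to 10 when the first dilution does not halve the foci, so r of 16 to 64 from that floor means titres of 160 to 640.

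| Infected / evaluable | r = 16 | r = 64 | Added seroconversion |
|---|---|---|---|
| 1 of 25 (placebo) | 1.12 | 1.18 | 4 points |
| 3 of 25 (placebo) | 1.39 | 1.65 | 12 points |
| 1 of 85 (vaccine) | 1.03 | 1.05 | at most 1.2 points |

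The last column assumes that the infected subject would not otherwise have seroconverted.

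**How likely.** P(at least one infection) = 1 − (1 − p)^n. At an assumed cumulative p of 5%, this is 72% for n = 25 and 99% for n = 85. At p = 1%, it is 22% and 57%. Over the short period to Visit 8, an assumed p of 0.2–0.5% with r = 16 shifts the GMT by only 0.6–1.4%.

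**The case against.** Several safeguards are real. Exclusion for a listed deviation is permissive. FAS results are also reported and bring back every dropped titre. Withdrawn subjects are asked to return for Visit 9 procedures. Infection is screened for at Visits 1 and 2, and an infection detected between doses can bar the second dose and lead to discontinuation (sections 5.3 and 5.4), which normally takes the subject out of the PPS. Part B plans within-group estimates with confidence intervals and tests no hypothesis, so no stated decision rests on the placebo GMT. An analysis plan, not shown, may add rules for titres after infection.

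These points limit the concern without removing it. The Visit 9 condition is definitional; the permissive wording governs only the deviation list. The FAS restores dropped titres but also keeps those drawn after infection or another vaccine. Infection after dose 2 breaches no instruction, so the blind meeting need not consider it. An analysis plan cannot use dates that were not collected.

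Stronger readings are tempting, and the documents do not support them:
- A reader might infer that results at Day 21, Week 26 and Week 52 are all biased by the completion rule. The Week 52 sample is itself taken at Visit 11, so completion to Visit 11 cannot drop it for a later event.
- A reader might infer that a coronavirus vaccine months later removes Day 21 titres from the main analysis. Main-study data are locked at Visit 9; this could happen only if membership were reset at the final lock, which the text neither says nor rules out.
- A reader might infer that only Visit 11 completers count at follow-up. The text says that they are analysed separately, not that they replace the Visit 9 set.
- A reader might infer that a mild infection never reaches the CRF. Subjects must report COVID-19 symptoms (sections 4.1.3.6 and 8.2), anosmia and ageusia are AESIs collected to Visit 11, and deviations are notified under section 5.6. What is missing is a required date for every subject.

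**Conclusion.** The concern holds in a limited form. The primary immunogenicity set discards valid Visit 8 titres on account of Visit 9. The follow-up set can lose Week 26 titres at the final analysis, and the prohibited-drug deviation can remove titres drawn before the deviation occurred. The certain cost is precision; bias is a risk that requires loss to be related to titre. At Day 21 after dose 2 the shift is about 1% in GMT, assuming 1–2% loss and titres half or double the others'.

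The larger exposure is at Weeks 26 and 52. Titres after infection following dose 2 stay in both sets, and titres after a non-study coronavirus vaccine stay in the FAS. The effect is greatest in the 25-subject placebo group and rests wholly on assumed infection counts and fold rises. The change is worth making because it is cheap and because the missing dates would be hard to recover later.

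**What to change.** In section 7.3.1, define the PPS for each visit: doses received as assigned up to that visit, a valid baseline, a sample at that visit, and only deviations that occurred before that sample. Delete the Visit 9 and Visit 11 completion conditions.

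Record on the CRF, for all subjects through Visit 11, the date of any confirmed SARS-CoV-2 infection and of any non-study coronavirus vaccine. Report Week 26 and Week 52 titres both with and without samples taken after those dates. Removing post-infection titres itself conditions on an event after randomisation, so neither version should stand alone. State also that undetected infections remain in both, because scheduled testing ends at Visit 2.

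The cost is a few sentences and two CRF fields. The number analysed will vary by visit and must be shown with each estimate.
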